#### Antimicrobial resistance

AMR will be monitored in CSIs in the Maradi region, which was selected as this region has not been involved in prior azithromycin MDA for child survival. Note that additional regions may be added if funds become available. CSIs will be randomly selected from among those selected for mortality monitoring in Maradi, with 20 randomly selected per arm using simple random sampling. AMR will be monitored at baseline and then approximately every 2 years. At baseline and 2 years, this will include 20 CSIs from the treated and delayed arms. At 4 years, this will include 20 CSIs each from the continue, stop, and original delayed arms. Population-based and clinic-based monitoring will be conducted.

Population-based monitoring will occur in 3 randomly selected communities within each of the selected CSIs. Pregnancy history data will be used to identify eligible children 1–59 months old, with 20 eligible children randomly selected for sample collections in each community. The study team will work with a local mobilizer to invite the selected group to a central location in the community for sample collection. Samples will be collected by trained personnel. Nasopharyngeal swabs, rectal swabs, and dried blood spots will be collected from all selected children with verbal consent from their guardian using procedures detailed in prior studies [12–14]. CHWs will visit the study community to complete treatment for that round once sample collections have been completed.

Clinic-based monitoring will occur in all selected CSIs. Children 1–59 months of age presenting with symptoms of respiratory illness, diarrhea/dysentery, and for well-child visits will be considered for inclusion, with the goal of including 30 children in each group. The WHO Integrated Management of Childhood Illness flowchart will be used to identify children presenting with illness [15]. Nasopharyngeal swabs will be collected from children with respiratory illnesses. Rectal swabs will be collected from children with diarrhea symptoms. Both nasopharyngeal and rectal swabs will be collected from healthy children.

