#### AMR

We plan to monitor 20 randomly selected CSIs per arm and 3 randomly selected communities per CSI, giving a total of 60 communities per arm. Within each community, 20 children will be randomly selected from the prior census to receive sample collections following procedures described above.Nasopharyngeal samples. A total of 120 communities (60 per arm) will provide approximately 80% power to detect a 7% absolute increase in the prevalence of macrolide-resistant pneumococcus isolates between arms. This assumes a 10% baseline prevalence of macrolide resistance, a community-level ICC of 0.045 estimated from MORDOR I 24-month data, and an alpha of 0.05 [12].Rectal samples: A total of 120 communities (60 per arm) will allow 80% power to detect a 1.4-fold increase in community mean normalized read number of genetic determinants of resistance to macrolides in rectal samples. This assumes an estimated ICC of 0.02 from the MORDOR I 24-month data, a standard deviation of 3.1 (on the logarithmic scale), and an alpha of 0.05 [12].

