### Statistical considerations

Statistical methods are described in detail for the primary mortality and AMR outcomes, which will involve intention-to-treat analyses.

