#### Analysis

The primary analysis for U5MR will be to compare the proportion of children who die before age 60 months between the two arms. The prior likelihood for mortality will be estimated using cluster-level data from the AVENIR I trial, using methods similar to the likelihood estimation [3]. We will model CSI-level U5MR using a generalized linear regression model with terms for treatment arm and baseline U5MR. CSIs should be of similar size, but if we find there are large differences in size, then we will consider weighting the regression by the number of measurements in each CSI. We will estimate the likelihood of the data from the fitted regression model. Note that the MOH committee and DSMC will review and approve the prior used past the second year of the trial, with options including incorporation of new results outside of AVENIR I and II, as well as down-weighting the prior from AVENIR I over time.

To estimate the posterior, beginning with the maximum likelihood estimate of all parameters obtained by the generalized linear model, we will choose particular values of the treatment effect b. For each such value, we maximize the likelihood with respect to the other parameters, yielding the profile likelihood function with respect to the single parameter b. We will multiply the profile likelihood by the prior to obtain the posterior distribution, normalized to ensure the posterior likelihood sums to 1. We will derive Bayesian credible intervals from the posterior derived in this way. Specifically, we will report the 95% central coverage interval and the estimated median. We will also estimate the probability of the null hypothesis under the posterior likelihood, and its complement (the probability MDA reduces the U5MR). Subgroup analyses for U5MR include region, child age, child sex, and community distance to the CSI. Note that for analyses of the second trial comparing the continue vs stop arms, the first 6 months will be excluded from analyses to allow for a washout period to account for lingering effects from prior treatment.

The Bayesian credible intervals of the U5MR will also be used to compare the measured mortality rate against the Sustainable Development Goal (SDG) targets (a secondary outcome). We will estimate the probability that the U5MR is at or below the SDG target using the area of the posterior distribution that falls at or below the SDG target.

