The primary analysis for resistance outcomes from community-based collection of nasopharyngeal (NP) swabs will be to compare the proportion of macrolide-resistant pneumococcal isolates between the two arms. If the laboratory is not able to grow pneumococcal isolates in at least 30% of the samples, we will use DNA testing instead.

The primary analysis for the community-based collection of rectal swabs will compare the community-level load of macrolide-resistant genetic determinants between the two arms. For both sets of samples, secondary analyses examining resistance in other classes of antibiotics, other age groups, and among individual antibiotic resistance genes will be conducted similarly.

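### The primary AMR comparisons name no baseline term, although Trial 1 measures baseline resistance in the same 20 CSIs per arm and the mortality model adjusts for baseline

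*Protocol article*

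**What the plan says.** The protocol article's Statistical considerations section opens with "Statistical methods are described in detail for the primary mortality and AMR outcomes".

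- **Mortality (Analysis).** CSI-level U5MR is analysed with a "generalized linear regression model with terms for treatment arm and baseline U5MR".
- **Resistance (Analysis).** The nasopharyngeal analysis "will be to compare the proportion of macrolide-resistant pneumococcal isolates between the two arms". The rectal-swab analysis compares community-level load between arms. No model, clustering method or covariate is named for either, and the secondary resistance analyses are to follow the same approach.
- **Data available (Outcome assessments, Antimicrobial resistance).** The timing is given as "AMR will be monitored at baseline and then approximately every 2 years". For Trial 1 the section adds: "At baseline and 2 years, this will include 20 CSIs from the treated and delayed arms". This reads as one set of CSIs measured twice.
- **Sample (Sample size and power, AMR).** The plan is for "20 randomly selected CSIs per arm and 3 randomly selected communities per CSI, giving a total of 60 communities per arm", and swabs come from 20 children per community.

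**The concern.** One section gives the baseline covariate for one primary domain and not for the other, after announcing that both are described in detail. A reader who follows the text would take mortality as baseline-adjusted and AMR as not.

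The gap falls where adjustment should help most. Mortality has 100 CSIs per arm across four regions; AMR has 20 per arm in Maradi alone, drawn by simple random sampling with no balancing on baseline resistance described. AMR is also the harm side of the decision that the Ministry of Health committee has to take. If the baseline values are not used, the AMR estimate carries between-CSI variation that data already in hand could partly remove.

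**Working it through.** **Inputs.** From the AMR sample-size paragraph: 60 communities per arm (20 CSIs x 3), 20 children per community, resistance 10% versus 17%, community-level ICC 0.045, alpha 0.05. Assumed: a two-sided test, since sidedness is not stated. Not in the article: the number of isolates per community and the baseline to year-2 correlation r.

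**Formulas.** For k clusters of m isolates per arm:
- design effect DE = 1 + (m - 1) x 0.045; effective n = k x m / DE
- power from the two-proportion normal formula (pooled variance under the null) on the effective n
- baseline adjustment: effective n divided by (1 - r²), so the standard error is multiplied by sqrt(1 - r²)
- ceiling on r: m x 0.045 / DE, for different children at each round and perfectly stable true cluster prevalence

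**The plan's own figure.** The article says 60 communities per arm "will provide approximately 80% power to detect a 7% absolute increase in the prevalence of macrolide-resistant pneumococcus isolates between arms". With all 20 children counted, DE = 1 + 19 x 0.045 = 1.855, effective n = 1200 / 1.855 = 647 per arm, and power is 95.8%. The stated 80% does not reproduce from the printed inputs. It does with about 8 isolates per community (a 40% yield, which is my assumption): DE = 1.315, effective n = 480 / 1.315 = 365, power 79.2%. That case is the more useful starting point.

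**Size of chance imbalance.** Between-cluster variance is 0.045 x 0.10 x 0.90 = 0.00405. The SD of the arm difference in true baseline prevalence is sqrt(2 x 0.00405 / 60) = 1.2 points if clustering is by community. It is sqrt(2 x 0.00405 / 20) = 2.0 points if the ICC is taken to apply to CSIs. The effect to be detected is 7 points.

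**Gain from adjustment, 10% versus 17%.**

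| Case | Power, unadjusted | r = 0.3 | r = 0.5 | At the ceiling on r |
|---|---|---|---|---|
| A. 60 communities, 8 isolates each (assumed) | 79.2% | above ceiling | above ceiling | 82.2% (r = 0.27) |
| B. 20 CSIs, 60 isolates each, ICC 0.045 assumed for CSIs | 74.8% | 78.7% | 85.9% | 97.4% (r = 0.74) |
| B'. As B, with 24 isolates each (40% yield) | 60.5% | 64.6% | 73.0% | 74.8% (r = 0.53) |
| C. 60 communities, all 20 children | 95.8% | 97.2% | above ceiling | 98.8% (r = 0.49) |

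In case A the standard-error multiplier at the ceiling is sqrt(1 - 0.274²) = 0.962, and the detectable difference at 80% power falls from 7.1 to 6.8 points. In case B it is 0.954 at r = 0.3 and 0.866 at r = 0.5, a gain of 3.9 to 11.1 points of power.

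**Cost.** With 40 CSIs, an arm-only comparison of CSI values has 38 residual degrees of freedom; the baseline term leaves 37.

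**The case against.** The strongest reply is that silence is not exclusion. The mortality paragraph opens with the same kind of sentence, a comparison of proportions between two arms, and only then gives a baseline-adjusted model. That wording alone therefore does not fix an unadjusted analysis. Covariates are ordinary content for a statistical analysis plan, the article refers to one, and it may already contain this term. All of this stands: a reader might infer that the plan has rejected baseline adjustment for AMR, and the article does not say so. What the reply does not remove is the mismatch inside one section that claims detail for both outcomes, or the fact that naming the term is a better specification using data already collected.

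A reader might also infer bias, with a baseline difference taken for an effect of MDA. That goes too far. CSIs are randomised 1:1 and the AMR CSIs are a simple random sample within arm, so the unadjusted estimate is unbiased and its standard error already allows for chance imbalance. Only precision is at stake.

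A larger gain is tempting too. At r = 0.6 the stated 7 points would become 7 x sqrt(1 - 0.36) = 5.6. But r = 0.6 exceeds the ceilings of 0.27, 0.49 and 0.53 above and is reachable only in case B, with an isolate from every child and near-perfect stability over two years. The 7-point start itself does not reproduce from the printed inputs.

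Finally, one might extend the remedy to Trial 2, using year-2 resistance as its baseline. Trial 2 draws a new sample of previously treated CSIs. Maradi has 216 CSIs, 25 of them delayed, leaving about 191. Under simple random sampling, the 40 continue and stop CSIs would include about 40 x 20 / 191 = 4 with a year-2 value. That is too few to support a covariate.

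**Conclusion.** The point holds for Trial 1, as a question of precision and consistency. The AMR text gives baseline resistance no role, while the mortality text uses its own baseline. Using it should tighten the AMR estimate unless r is close to zero.

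The gain is modest to moderate: about 3 points of power at the ceiling in case A, and about 4 to 11 points in case B with r from 0.3 to 0.5. Both ranges rest on assumptions that the article does not settle: the isolate yield, whether the ICC of 0.045 carries over to CSIs, and r itself. Nor does it say whether the same three communities per CSI are resampled. If they are not, and most clustering lies between communities within a CSI, the gain would be smaller still. The rectal-load gain scales by the same sqrt(1 - r²) factor but is not sized here.

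**What to change.** For Trial 1, state that the primary nasopharyngeal-resistance and log-scale rectal-load analyses regress the CSI-level year-2 value on arm plus the CSI's own baseline value, in line with the U5MR model. Keep the unadjusted comparison as a sensitivity analysis. The CSI is the right level because it is the randomised unit and because resampling of the same communities is not stated.

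Fix this before year-2 AMR data are analysed, since a covariate added afterwards would look data-driven. If the statistical analysis plan already says this, one clause in the Analysis section is enough. The cost is one model term, one degree of freedom and no new data collection. Leave Trial 2 as it is on this point.

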### Randomization, adaptation, and masking

#### Randomization unit and monitoring sample

The randomization unit for this trial is the CSI, which is a primary health care center with an average catchment area of approximately 20 communities (*grappes)*, each of which includes an average of approximately 100 children under 5. A random sample of 200 CSIs eligible for the program will be selected for participation in the trials as a stratified sample of 50 CSIs from each of the four regions launching the program in year 1: Dosso, Tahoua, Maradi, and Zinder. Trial 1 will include this initial sample of 200 CSIs, which will be randomized 1:1 to receive the intervention or to receive delayed treatment. After 2 years, the 100 delayed CSIs will be treated by the program. For Trial 2, we will select another random sample of 200 CSIs from among those previously treated, again stratified by region. Note that the sample sizes included in Trial 2 are subject to the adaptation as described in the next section.

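### AMR power counts 60 communities per arm and the rectal comparison is set at community level, although CSIs are randomised; the stated 80% power also does not follow from its inputs

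*Protocol article*

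**What the plan says.** **Unit of randomisation.** Protocol article, Randomization unit and monitoring sample: "The randomization unit for this trial is the CSI".

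**Sampling.** Outcome assessments, Antimicrobial resistance: "Population-based monitoring will occur in 3 randomly selected communities within each of the selected CSIs". The AMR part of Sample size and power gives the numbers as follows: "We plan to monitor 20 randomly selected CSIs per arm and 3 randomly selected communities per CSI, giving a total of 60 communities per arm". It then sets the sample of children in these words: "Within each community, 20 children will be randomly selected from the prior census".

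**Power.** The same AMR section says for nasopharyngeal swabs: "A total of 120 communities (60 per arm) will provide approximately 80% power to detect a 7% absolute increase". It adds "This assumes a 10% baseline prevalence of macrolide resistance", a community-level ICC of 0.045 and alpha 0.05. For rectal swabs it gives 80% power for a 1.4-fold increase with 60 communities per arm, an ICC of 0.02 (level not named), and an SD of 3.1 on a log scale whose base is not given. No CSI-level correlation appears in either calculation.

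**Analysis.** For rectal swabs: "The primary analysis for the community-based collection of rectal swabs will compare the community-level load of macrolide-resistant genetic determinants between the two arms". For nasopharyngeal swabs the section compares the proportion of resistant isolates between arms and names no unit. No model, test or clustering method is named for either AMR outcome. The mortality outcome, by contrast, is modelled at CSI level in the same section, and its power uses cluster-level means.

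**The concern.** The randomised design has 20 independent units per arm for resistance, not 60. Communities in one CSI are allocated together. The document also gives reason to expect their results to be correlated: local CSI leaders supervise the health workers (Implementation outcomes), and the Discussion expects more varied delivery and coverage across settings than in the earlier trials. A community-level ICC describes the similarity of children within a community. It says nothing about the similarity of communities within a CSI.

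If the comparison is made on 60 v 60 community values without a CSI term, the standard error is too small whenever that second correlation is above zero, and the false-positive rate exceeds 5%. This matters because resistance is the harm weighed against the mortality benefit, and the Ministry committee's decision to continue, expand or stop the programme depends on it.

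**Working it through.** **Inputs from the AMR power section.** 60 communities x 20 children = 1200 children per arm; nasopharyngeal 10% v 17%, ICC 0.045; rectal 1.4-fold, ICC 0.02, log SD 3.1; alpha 0.05.

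**Assumptions.** The test is two-sided. The correlation c between children in different communities of one CSI (the CSI-level ICC) is not given, so it is varied from 0 up to the stated ICC. Isolate yield is not given; 100% and 40% are shown. Log base is not given; natural log and log2 are shown.

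**Step 1: the stated nasopharyngeal power.** Design effect = 1 + 19 x 0.045 = 1.855, so effective n = 1200/1.855 = 647 per arm.

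Power = Φ[(0.07√647 − 1.96√(2 x 0.135 x 0.865)) / √(0.10 x 0.90 + 0.17 x 0.83)] = Φ[(1.780 − 0.947)/0.481] = Φ(1.73) = 96%, not about 80%.

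With a 40% yield there are 8 isolates per community: design effect 1 + 7 x 0.045 = 1.315, effective n = 480/1.315 = 365, power 79%. The stated figure is therefore reached at roughly 40% yield, which the document does not state. It gives only a 30% threshold for switching to DNA testing.

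**Step 2: the stated rectal power.** Design effect = 1 + 19 x 0.02 = 1.38, effective n = 870, SE = 3.1√(2/870) = 0.149.
- Natural log: Φ(0.336/0.149 − 1.96) = 62%.
- Log2: Φ(0.485/0.149 − 1.96) = 90%.

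Log10 gives 16%. One-sided tests give 98% (nasopharyngeal, all children), 73% (rectal, natural log) and 95% (rectal, log2). None returns 80%.

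**Step 3: power with CSI clustering.** For m children per community, design effect = 1 + (m − 1) x ICC + 2m x c.

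| CSI ICC c | NP, all 20 children | NP, 8 isolates | Rectal, natural log | Rectal, log2 |
|---|---|---|---|---|
| 0 | 96% | 79% | 62% | 90% |
| 0.01 | 92% | 74% | 51% | 82% |
| 0.02 | 87% | 70% | 44% | 74% |
| 0.045 | 75% | 60% | n/a | n/a |

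With all children counted, nasopharyngeal power falls below 80% only above c of about 0.034. Rectal power on log2 does so above about 0.012.

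**Step 4: type I error of a community-level test that ignores CSI.** The variance of a community mean, as a share of the total, is v = (1 + (m − 1) x ICC)/m. The correlation of two community means in one CSI is r = c/v. The true variance of an arm mean is (v/60)(1 + 2r), while the naive estimate averages (v/60)(1 − 2r/59). Hence

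type I = 2[1 − Φ(1.96√((1 − 2r/59)/(1 + 2r)))].

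- Rectal, m = 20: v = 1.38/20 = 0.069. At c = 0.005, r = 0.072 and type I = 6.7%. At 0.010, r = 0.145 and 8.5%. At 0.015, r = 0.217 and 10.3%. At 0.020, r = 0.290 and 12.1%. A 20,000-replicate simulation of 40 CSIs x 3 communities gave 7.0%, 8.5% and 10.5% at the first three values; the 20 v 20 CSI-level test held 5.1-5.2%.
- Nasopharyngeal, m = 20: v = 1.855/20 = 0.0928. At c = 0.01, r = 0.108 and 7.6%. At 0.02, r = 0.216 and 10.3%.
- Nasopharyngeal, m = 8: v = 1.315/8 = 0.164. At c = 0.01, r = 0.061 and 6.45%. At 0.02, r = 0.122 and 7.9%.

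**The case against.** The strongest reply is that no sentence says communities will be treated as independent. Community-level load may name only the summary measure, which is compatible with a mixed model containing CSI effects or a permutation over CSIs. The mortality analysis opens in equally general words and then specifies a CSI-level model. A separate statistical analysis plan is mentioned and not shown. The Missing data section uses communities loosely for the 200 CSIs.

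Much of this stands. A reader might infer that all four primary AMR comparisons will have inflated false-positive rates. The document does not support that: the nasopharyngeal comparison names no unit, no AMR model is given, and the inflation needs a CSI-level correlation that is not stated.

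A reader might also infer that the 80% power is overstated. That is not established either. With all children counted, nasopharyngeal power exceeds 80% even with a moderate CSI correlation, and the rectal figure is too high or too low depending on the log base.

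It is equally unsupported to say that communities in one CSI share health workers or antibiotic supply; the text supports shared supervision only. Nor should the largest type I inflation be paired with the sub-80% nasopharyngeal power at CSI ICC 0.01-0.02: they arise under different yields.

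What the reply does not remove is the power basis, which this document states itself, and the stated level of the rectal comparison. The loose usage elsewhere does not help, because the AMR power section explicitly counts 60 communities inside 20 CSIs. The Statistical considerations section also claims detail for the AMR outcomes, so the omission cannot be wholly deferred.

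**Conclusion.** The point holds in a limited form. The AMR power omits the level at which the trial is randomised, and the rectal primary comparison is worded below that level. For nasopharyngeal swabs the unit is simply open.

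The error-rate consequence is conditional on a community-level test without a CSI term and on an assumed CSI ICC. It is about 7-10% for rectal swabs at 0.005-0.015 (12% at 0.02). For nasopharyngeal swabs at 0.01-0.02 it is about 7.6-10% with 20 children per community, or 6.4-7.9% with 8. If the CSI ICC is zero, there is no inflation.

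Independently of CSI clustering, the stated 80% cannot be recovered from the stated inputs for either outcome without supplying an isolate yield or a log base. The direction of the discrepancy depends on those missing inputs, so the figure is unverified rather than shown to be too high.

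**What to change.** **Analysis section.** State that both AMR outcomes are analysed with the CSI as the unit: 20 v 20 CSI summaries, by t-test on 38 df or permutation over CSIs. Alternatively, specify a mixed model with CSI and community random effects. Fix the choice before the AMR results are known.

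**AMR power section.** Recompute and restate the detectable differences for 20 CSIs per arm x 3 communities x 20 children. State the assumed CSI-level ICC (with a range if no estimate exists), the expected isolate yield, the log base of the SD and the sidedness of the test.

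**Optional.** In Trial 1, adjusting for the CSI's baseline resistance could improve precision, since AMR is measured at baseline. This is an efficiency gain, not a correction.

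**Cost.** Changed wording and a possibly less favourable power statement. No new data, sites or samples are needed.
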